## **2. OBJECTIVES AND HYPOTHESIS**

### **2.1. Objectives**

#### **Primary Objectives**

The primary objectives are:

- To determine the efficacy of TMC435 plus PegIFN $\alpha$ -2a and RBV when administered for 12 weeks in treatment-naïve subjects with chronic genotype 1 HCV infection, as measured by the proportion of subjects with sustained virologic response 12 weeks after planned end of treatment (SVR12).
- To assess the safety and tolerability of TMC435 plus PegIFN $\alpha$ -2a and RBV when administered for 12 weeks in treatment-naïve subjects with chronic genotype 1 HCV infection

#### **Major Secondary Objectives**

Major secondary objectives are:

- To determine the efficacy of TMC435 plus PegIFN $\alpha$ -2a and RBV when administered for 12 weeks in treatment-naïve subjects with chronic genotype 4 HCV infection, as measured

by the proportion of subjects with sustained virologic response 12 weeks after planned end of treatment (SVR12).

- To assess the safety and tolerability of TMC435 plus PegIFN $\alpha$ -2a and RBV when administered for 12 weeks in treatment-naïve subjects with chronic genotype 4 HCV infection

Further major secondary objectives are in subjects with genotype 1 or genotype 4 HCV infection (separately per genotype):

- To determine the proportion of subjects who achieve virologic response at Week 2 (W2VR) and the proportion of subjects who achieve RVR.
- To determine the relationship between W2VR and SVR12 and between RVR and SVR12.
- To determine the efficacy of TMC435 plus PegIFN $\alpha$ -2a and RBV for 12 weeks followed by 12 weeks of PegIFN $\alpha$ -2a and RBV (i.e., a total treatment duration of 24 weeks), as measured by the proportion of subjects with SVR12.
- To determine the efficacy of TMC435 plus PegIFN $\alpha$ -2a and RBV after a total treatment duration of 12 weeks, as measured by the proportion of subjects with sustained virologic response 24 weeks after planned end of treatment (SVR24).
- To determine the efficacy of TMC435 plus PegIFN $\alpha$ -2a and RBV for 12 weeks followed by 12 weeks of PegIFN $\alpha$ -2a and RBV (i.e., a total treatment duration of 24 weeks), as measured by the proportion of subjects with SVR24.
- To evaluate the evolution of HCV RNA levels at regular intervals during treatment and after planned end of treatment.

and for both genotypes combined:

- To evaluate impact of HCV or its treatment on patient reported symptoms and functioning using a new patient reported outcomes tool, the Hepatitis C Symptom & Impact Questionnaire (HCV-SIQ) and four well-validated PRO instruments measuring severity and impact of fatigue (Fatigue Severity Scale, FSS), depressive symptoms (Center for Epidemiologic Studies Depression Scale, CES-D), time missed from work and impairment in daily activities (Work Productivity and Activity Impairment, WPAI: Hepatitis C), and health status (EuroQol 5 Dimension, EQ5D).

### Definitions

Sustained virologic response 12 weeks after planned end of treatment (SVR12) will be defined as undetectable HCV RNA ( $< 25$  IU/mL undetectable) at the actual end of treatment and 12 weeks after the planned end of treatment.

Rapid virologic response (RVR) will be defined as HCV RNA  $< 25$  IU/mL undetectable measured 4 weeks after start of treatment.

Virologic response at Week 2 (W2VR) will be defined as HCV RNA  $< 25$  IU/mL (detectable or undetectable) measured 2 weeks after start of treatment.

## Exploratory Objectives

The exploratory objectives in subjects with genotype 1 or genotype 4 HCV infection are:

- to evaluate the measurement properties of the HCV-SIQ
- to explore alternate scoring of the HCV-SIQ (e.g., total score, symptom scores by body system).

## 2.2. Hypothesis

In this study, the response rate (SVR12) in subjects with genotype 1 HCV infection eligible for and assigned to 12 weeks of treatment is expected to be superior to the minimally acceptable response rate of 80%.

## 3. STUDY DESIGN AND RATIONALE

### 3.1. Overview of Study Design

This, multicenter, international study will evaluate the efficacy, tolerability, and safety of 12-week triple therapy with TMC435 plus PegIFN $\alpha$ -2a and RBV in treatment-naïve adult subjects with genotype 1 or genotype 4 chronic HCV infection and fibrosis stage equivalent to F0-F2. A target of 150 subjects with genotype 1 chronic HCV infection and 75 subjects with genotype 4 chronic HCV infection will be assigned to treatment in this study.

In an attempt to enroll similar percentages of the 3 host *IL28B* genotypes (CC, CT or TT) as were enrolled in the ongoing Phase 3 TMC435 studies, the sponsor will make all effort to respect the following maximum caps for enrolment of each *IL28B* genotype for subjects with genotype 1 or genotype 4 HCV infection separately:

- a maximum of 35% of subjects with host *IL28B* genotype CC (i.e., maximum 35% *IL28B* CC among subjects with genotype 1 HCV infection and maximum 35% *IL28B* CC among subjects with genotype 4 HCV infection);
- a maximum of 55% of subjects with host *IL28B* genotype CT (i.e., maximum 55% *IL28B* CT among subjects with genotype 1 HCV infection and maximum 55% *IL28B* CT among subjects with genotype 4 HCV infection);
- a maximum of 18% of subjects with host *IL28B* genotype TT (i.e., maximum 18% *IL28B* TT among subjects with genotype 1 HCV infection and maximum 18% *IL28B* TT among subjects with genotype 4 HCV infection).

In addition, within subjects infected with genotype 1 HCV, the sponsor seeks a balance between HCV genotypes 1a and 1b, therefore all effort will be made to cap enrolment of HCV genotype 1a at:

- a maximum of 50% of subjects infected with HCV genotype 1a.

Procedures to manage the distribution of the HCV genotype 1 subtypes and the host *IL28B* subtypes will be communicated to participating investigators at study initiation.

All subjects will start treatment at baseline (Day 1) and will receive triple therapy consisting of TMC435 plus PegIFN $\alpha$ -2a and RBV for 12 weeks. Total anti-HCV treatment duration will be response-guided based on HCV RNA levels at Week 2, Week 4, and Week 8 as follows:

- Subjects will qualify for a total treatment duration of only 12 weeks (ie all anti-HCV treatment is discontinued after week 12) if the following criteria are met: if HCV RNA value is
  - < 25 IU/mL (detectable or undetectable) at Week 2,  
AND
  - < 25 IU/mL undetectable at Week 4,  
AND
  - < 25 IU/mL undetectable at Week 8.
- if HCV RNA is above the threshold defined above at any of the 3 time points, subjects will continue PegIFN $\alpha$ -2a and RBV until Week 24.

A diagram of the study design is provided in Figure 1.

Regardless of treatment duration, endpoint to evaluate efficacy will be SVR12.

The treatment continuation criteria will at all times be overruled if a subject meets any of the virologic stopping criteria outlined below. Subjects meeting any of the following criteria will be required to discontinue all treatment:

- Week 4: HCV RNA  $\geq$  25 IU/mL
- Week 12: HCV RNA  $\geq$  25 IU/mL OR < 25 IU/mL detectable
- a confirmed increase of  $> 1 \log_{10}$  IU/mL in HCV RNA level from the lowest level reached, or a confirmed HCV RNA level of  $> 100$  IU/mL in subjects whose HCV RNA level had previously been  $< 25$  IU/mL while on study drugs.

Detectable HCV RNA after previous undetectability should be confirmed by a confirmatory HCV RNA measurement within 2 weeks after receipt of the detectable HCV RNA value. Treatment should only be discontinued after HCV RNA detectability is confirmed (see Section 6.3, Virologic Stopping Criteria for further details).

HCV RNA will be measured centrally and the results will be communicated to the investigational sites. It will be the investigator's responsibility to take the necessary actions regarding the discontinuation of therapy in case a virologic stopping rule has been met.

**Figure 1: Schematic Overview of the Study**

**All subjects:** 12 weeks of triple therapya; stop all therapy after Week 12 if  
HCV RNA < 25 IU/mL (detectable or undetectable) at Week 2 AND  
< 25 IU/mL undetectable at Week 4 AND  
< 25 IU/mL undetectable at Week 8;  
otherwise continue treatment in Extension

[figure not shown]**Treatment Extension**

If HCV RNA at Week 2, 4 and 8 does not meet the above-outlined criteria for treatment stop at Week 12, the subject should continue PegIFN/RBV until Week 24a

[figure not shown]

a unless a virologic stopping rule is met, see Section 6.3, Virologic Stopping Criteria for further details

b primary endpoint

c secondary endpoint

TMC435 will be taken as oral capsules of 150 mg. PegIFN $\alpha$ -2a and RBV will be given as Pegasys and Copegus (see Section 6.2, Timing of Dosing for further details). Pegasys and Copegus will be administered according to the manufacturer's prescribing information. Pegasys (180  $\mu$ g once weekly) will be administered as weekly subcutaneous (SC) injections of 0.5 mL. The total daily dose of Copegus is weight-dependent. If body weight is < 75 kg, the total daily dose is 1000 mg, administered as 400 mg (2 tablets of 200 mg, morning intake) and 600 mg (3 tablets of 200 mg, evening intake). If body weight is  $\geq$  75 kg, the total daily dose is 1200 mg, administered as 2 x 600 mg (3 tablets of 200 mg per intake, morning and evening).

The study will be conducted in 3 phases: a screening phase of maximum 6 weeks, a treatment phase extending from Day 1 (baseline) up to 12 or 24 weeks depending on the response to treatment, and a posttreatment follow-up period of 24 weeks after the subject's last planned dose of study drug. The duration of the subject's participation (excluding screening phase) will vary between 36 weeks and 48 weeks, depending on the response to treatment.

Subjects should maintain the study visit schedule during treatment interruptions or after premature treatment discontinuation as outlined in the Time and Events Schedule. Additional unscheduled visits may be performed for safety or tolerability reasons if needed.

Interim analyses will be conducted (refer to Section 11.5, Interim Analyses).

The key efficacy evaluation will be plasma HCV RNA levels (see Section 9.2.1, Evaluations). Safety evaluations will include the monitoring of AEs, physical examinations, vital sign measurements, clinical laboratory tests, and pregnancy testing. Patient-reported outcomes (PROs) will also be assessed.

A pharmacogenomic blood sample will be collected to allow for host *IL28B* genotyping. This pharmacogenomic blood sample is mandatory and will be collected from all subjects who consent to participate in the study.

### **3.2. Study Design Rationale**

#### **Blinding, Control, Study Phase/Periods, Treatment Groups**

This is a study without an active or placebo control. No randomization or blinding procedures are applicable.

#### **Patient Reported Symptoms and their Impact**

Severity and impact of symptoms before, during and after treatment provide important information for patients and physicians about the tolerability of treatments beyond what is known from AE reports. Prospectively collecting information about symptoms and their impact gives physicians better information to advise patients about what to expect during treatment and how long any symptoms or functional problems that may occur during treatment are likely to last. Patients are better able to anticipate and persist with treatment when symptoms occur if information about duration, severity and impact of symptoms from clinical studies can be provided.

Adding TMC435 to PegIFN $\alpha$ -2a/RBV has not been found to increase symptoms or functional limitations beyond what patients experience with PegIFN $\alpha$ -2a and RBV. TMC435 Phase 2 and Phase 3 studies used PRO measures to study two of the most common symptoms associated with PegIFN $\alpha$ -2a/RBV treatment: fatigue and depressive symptoms. Data from the PRO measures documented the duration and intensity of symptoms subjects experienced based on their own ratings throughout treatment and follow-up. The prospective collection of the PRO symptom data provided valuable information beyond what was known based on AE frequency and severity reports.

For this study, 5 PRO measures will be administered during study visits to document quality of life and symptom onset, duration, severity, and impact from the subject's perspective. The HCV-SIQ asks subjects to rate 26 symptoms associated with HCV or its treatment and how symptoms impacted the subjects' life during the prior week. This questionnaire provides a simple tool for monitoring symptoms during HCV treatment and follow-up that may be suitable for clinical

management of patients as well as for clinical research. To help evaluate the validity of the HCV-SIQ, 4 PRO questionnaires that have been used extensively in prior HCV studies will also be collected. The Fatigue Severity Scale (FSS) will be used to document fatigue severity and impact of fatigue on subjects' daily lives. The Center for Epidemiologic Studies Depression Scale (CES-D), a brief assessment that asks subjects to rate how often in the past week they experienced 20 symptoms associated with depressive illness, will be used to assess depressive symptom severity. The Work Productivity and Activity Index for Hepatitis C (WPAI: Hepatitis C) will be used to measure the impact of HCV on time missed from work (absenteeism), reduced performance while at work (productivity impairment), and impairment in daily activities without regard to employment status. Finally, the EuroQol 5 Dimension (EQ5D) scale and overall health status will be used to measure the impact of HCV and its treatment on health-related quality of life (HRQoL). Together, the PRO instruments collected in this study are included to help better characterize the symptoms patients experience with HCV treatment, the impact symptoms have on patient's lives, and to evaluate the validity and reliability of HCV-SIQ for use in future HCV studies.

#### **4. SUBJECT POPULATION**

Screening for eligible subjects will be performed within 6 weeks before administration of the study drug.

The inclusion and exclusion criteria for enrolling subjects in this study are described in the following 2 subsections. If there is a question about the inclusion or exclusion criteria below, the investigator should consult with the appropriate sponsor representative before enrolling a subject in the study.

For a discussion of the statistical considerations of subject selection, refer to Section 11.2, Sample Size Determination.

##### **4.1. Inclusion Criteria**

Each potential subject must satisfy all of the following criteria to be enrolled in the study. Exceptional and limited retesting of abnormal screening values that lead to exclusion is allowed only once using an unscheduled visit during the screening period (to reassess eligibility). This should only be considered if there is no anticipated impact on subject safety. Refer to Section 9.1.2 for full details.

1. Subject must be a man or woman 18 to 70 years of age, inclusive, prior to the baseline visit.
2. Subject must have confirmed chronic HCV infection as documented by a positive anti-HCV antibody test, or positive HCV RNA test at least 6 months prior to screening, or positive HCV genotyping test at least 6 months prior to screening.

3. Subject's liver disease stage must be equivalent to Metavir Score F0-F2 (no fibrosis, or portal fibrosis without or with few septa) as confirmed by a liver biopsy performed within 2 years prior to screening or by non-invasive determination of liver disease stage (by transient elastography) performed within 6 months prior to screening. Non-invasive staging assessments include FibroScan™ or MR-Elastography.

Note: The Metavir scoring system is provided in Attachment 1. For non-invasive fibrosis assessment, FibroScan™ should be < 8 kPa and MR-Elastography should be < 3.1 kPa. For any other transient elastography method (eg, Shear Wave Elastography), please contact the sponsor for advice.

4. Subject with liver disease stage equivalent to Metavir Score F2 and without liver biopsy performed within 2 years prior to screening must have undergone liver imaging (ultrasound, computed tomography [CT], or magnetic resonance imaging [MRI]) within 6 months prior to the Screening visit (or between the Screening and Baseline/Day 1 visits) with no findings suspicious of hepatocellular carcinoma.
5. Subject must have genotype 1 or genotype 4 HCV infection (confirmed at screening).
6. Subject's plasma HCV RNA must be > 10000 IU/mL at screening.

Note: Retesting of HCV RNA to assess eligibility will be allowed once, using an unscheduled visit during the screening period.

7. Subject has not received prior treatment for hepatitis C with any approved or investigational drug.
8. Before screening, a woman must be either:

- Not of childbearing potential: postmenopausal (> 45 years of age with amenorrhea for at least 12 months or any age with amenorrhea for at least 6 months and a serum follicle stimulating hormone (FSH) level > 40 IU/mL); permanently sterilized (e.g., tubal occlusion, hysterectomy, bilateral salpingectomy); or otherwise be incapable of pregnancy,
- Of childbearing potential and practicing two different highly effective methods of birth control (including at least one barrier method) consistent with local regulations regarding the use of birth control methods for subjects participating in clinical studies: e.g., established use of oral, injected or implanted hormonal methods of contraception; placement of an intrauterine device (IUD) or intrauterine system (IUS); barrier methods: condom with spermicidal foam/gel/film/cream/suppository or occlusive cap (diaphragm or cervical/vault caps) with spermicidal foam/gel/film/cream/suppository; male partner sterilization (the vasectomized partner should be the sole partner for that subject); true abstinence (when this is in line with the preferred and usual lifestyle of the subject).

Note: If the childbearing potential changes after start of the study (e.g., woman who is not heterosexually active becomes active, premenarchal woman experiences menarche) a woman must begin 2 highly effective methods of birth control, as described above.

9. A woman must have a negative serum  $\beta$ -human chorionic gonadotropin ( $\beta$ -hCG) test at screening and women of childbearing potential must have a negative urine pregnancy test before first dose of study drug.
10. A man who is sexually active with a woman of childbearing potential and has not had a vasectomy must agree to use two different highly effective methods of birth control (including at least one barrier method). A man who is sexually active with a woman of childbearing potential and has had a vasectomy must agree to use a barrier method of birth control e.g., either condom with spermicidal foam/gel/film/cream/suppository or partner with occlusive cap (diaphragm or cervical/vault caps) with spermicidal foam/gel/film/cream/suppository. All men must also not donate sperm during the study and for 6 months (or longer if dictated by local regulations) after the last dose of RBV.
11. Subject must be willing and able to adhere to the prohibitions and restrictions specified in this protocol.
12. Each subject must sign an informed consent form (ICF) indicating that he or she understands the purpose of and procedures required for the study and are willing to participate in the study.
13. Subject with genotype 4 HCV infection must have a body mass index (BMI) of  $\leq 32 \text{ kg/m}^2$ .

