#### Footnotes

- a Screening within 6 weeks of planned baseline visit. Prolongation of this period for legitimate reasons may be allowed upon written approval from the sponsor. Screening assessments can be done during the screening period and need not necessarily be done at the same moment. When the cap for enrolment has been reached for a specific IL28B genotype, stepwise screening can be performed, ie after signing of the ICF, IL28B screening can be done first. If the lab results show that the subject has another IL28B genotype than the one for which the enrolment cap was reached, further screening assessments can be undertaken.. Upon confirmation of all eligibility parameters, the baseline visit can take place.
- b The baseline visit should take place as soon as all details to confirm eligibility have been obtained.
- c Subjects who prematurely discontinue all study medication (TMC435/PegIFN $\alpha$ -2a/RBV) should switch to the visit schedule as laid out in Time and Events Schedule - Part 4 (unless the subject withdraws consent).
- d Including integrated consent for mandatory *IL28B* polymorphism analysis
- e Minimum criteria for the availability of documentation supporting the eligibility criteria are described in Section 17.4, Source Documentation.
- f Confirmation of liver disease status either by liver biopsy or non-invasive method as described in Section 4.1, Inclusion Criteria. If results are available from either a liver biopsy performed within 2 years prior to the screening visit or from non-invasive confirmation of the liver condition (by transient elastography) performed within 6 months prior to the screening visit, this assessment does not need to be repeated.
- g After the results have been obtained, all remaining blood samples for *IL28B* genotyping will be destroyed.
- h Only for subjects infected with genotype 4 HCV. If the schistosomiasis antibody test is positive, a schistosomiasis antigen blood test or rectal snip should be performed. Subjects with a positive schistosomiasis antigen blood test or positive rectal snip are excluded from study participation .
- i Alpha-fetoprotein (AFP) will be tested for all subjects. Follicle-stimulating hormone (FSH) will be tested for female subjects who are postmenopausal for less than 2 years.
- j Free thyroxine (T4) and free triiodothyronine (T3) will be assessed if TSH is abnormal.

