a The homeostasis model assessment for insulin resistance (HOMA IR) index will be derived from insulin and glucose (fasted) test results at baseline, Week 4, Week 12, Week 24, Week 36, and Week 48 (as applicable).

b Safety sampling will also include a TSH test at screening, and thereafter every 12 weeks after the start of study treatment until the end of PegIFN $\alpha$ -2a and RBV treatment. In case of clinically significant abnormal TSH levels, reflex testing for free T3 and free T4 will be performed.

c The biochemistry sample taken at screening will include testing for glycosylated hemoglobin (HbA1c) and ANA.

The central laboratory will estimate the creatinine clearance (CLcr) according to the formula derived from the Modification of Diet in Renal Diseases (MDRD) study.

A midstream urine sample must be provided for local urinalysis by dipstick. If there are clinically relevant abnormalities in the investigator's opinion, further urinalysis should be done locally (e.g., sediment analysis including RBC, WBC, casts). Any clinically relevant findings from this local analysis should be reported as an AE.

- Urinalysis

- Dipstick**

- specific gravity
  - pH
  - glucose
  - protein
  - blood
  - ketones
  - bilirubin
  - urobilinogen
  - nitrite
  - leukocyte esterase

- Serum (at screening, all female subjects) and urine (at other time points, female subjects of childbearing potential only) pregnancy testing will be performed. Extra pregnancy test kits will be given if more than 4 weeks between two consecutive study visits to perform a pregnancy test at home. The results of the urine pregnancy test should be recorded in the eCRF and in the subject's medical records.
- At screening, serology for HIV-1 and HIV-2 antibody, hepatitis A immunoglobulin M (IgM), HBsAg, and anti-HCV antibody will be performed.
- At the screening visit, an additional midstream urine sample must be provided for a urine drug screen. The drug screening involves analysis for amphetamines, benzodiazepines, cocaine, cannabinoids, barbiturates and opioids.
- At screening a schistosomiasis antibody test will be performed. If the schistosomiasis antibody test is positive, a schistosomiasis antigen blood test or rectal snip should be performed.
- At the screening visit, AFP will be tested for all subjects. FSH will be tested for female subjects who are postmenopausal for less than 2 years.

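### The FSH threshold in inclusion criterion 8 is printed in a unit that is probably a 1000-fold slip, and the FSH testing schedule does not cover the women whose classification depends on it

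*Protocol*

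**What the plan says.** Section 4.1, criterion 8, opens with "Before screening, a woman must be either" and then offers two alternatives.

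The first is not being of childbearing potential. A woman can meet it by being postmenopausal, defined as "> 45 years of age with amenorrhea for at least 12 months or any age with amenorrhea for at least 6 months", the second limb being joined to a "serum follicle stimulating hormone (FSH) level > 40 IU/mL". She can also meet it by being "permanently sterilized (e.g., tubal occlusion, hysterectomy, bilateral salpingectomy); or otherwise be incapable of pregnancy".

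The second alternative is to be of childbearing potential and using two highly effective methods of birth control, at least one of them a barrier method.

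Two other places say who has FSH measured at screening. Section 9.5.2: "FSH will be tested for female subjects who are postmenopausal for less than 2 years". Footnote i to the Time and Events Schedule, Part 1: "Follicle-stimulating hormone (FSH) will be tested for female subjects who are postmenopausal for less than 2 years".

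The threshold appears only in criterion 8. No other part of the protocol gives an FSH unit, reference range or second cut-off.

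**The concern.** There are two separate problems.

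The first is the unit. A cut-off in IU per millilitre is 1000 times the same number in IU per litre. Serum FSH is ordinarily reported in IU/L, numerically the same as mIU/mL. IU/mL is the unit the protocol uses for HCV RNA, including in criterion 6 of the same list, so a carry-over is plausible.

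The second is that the set of women tested differs from the set whose status turns on the test. The criterion selects by age and a minimum duration of amenorrhea. The schedule selects by a maximum time since menopause and ignores age.

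The classification matters because ribavirin is contraindicated in pregnancy. It decides who has the scheduled urine pregnancy tests after screening and who must use two contraceptive methods up to 6 months after the last ribavirin dose (Section 4.3).

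**Working it through.** **Unit.** The input is the cut-off in criterion 8.

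- 40 IU/mL × 1000 mL/L = 40,000 IU/L = 40,000 mIU/mL.
- If IU/L or mIU/mL was meant, the intended value is 40 IU/L, and 40,000 / 40 = 1000.
- If the printed unit was meant, the ratio is 1 and there is no slip. The protocol has no second FSH figure that would settle this. The choice rests on the laboratory convention, which is an assumption here.

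**Schedule against criterion.** Take a woman who is neither sterilized nor otherwise unable to conceive, and treat time since menopause as the duration of amenorrhea. In the natural reading, FSH belongs only to the 6-month limb of the definition. The need for FSH comes from criterion 8 and the scheduling from footnote i and Section 9.5.2.

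| Age | Amenorrhea | FSH needed for postmenopausal status | FSH scheduled | Match |
|---|---|---|---|---|
| ≤ 45 | 6 to < 12 months | yes | yes | yes |
| ≤ 45 | 12 to < 24 months | yes | yes | yes |
| ≤ 45 | ≥ 24 months | yes | no | **needed, not scheduled** |
| > 45 | 6 to < 12 months | yes | yes | yes |
| > 45 | 12 to < 24 months | no | yes | **scheduled, not needed** |
| > 45 | ≥ 24 months | no | no | yes |

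For example, a 43-year-old with 3 years of amenorrhea needs an FSH value to be called postmenopausal, and none is scheduled.

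The sentence can also be read with FSH attached to both limbs. Then every row needs FSH. The over-45 row at 12 to < 24 months becomes a match, and the over-45 row at ≥ 24 months becomes a second gap. The gap at age 45 or younger remains under either reading.

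Even the matching rows where FSH is needed have a logical difficulty. The schedule tests women already called postmenopausal, but for these women FSH is what decides whether they are. A site has to presume the answer in order to order the test.

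**Numbers affected.** The planned total is 150 + 75 = 225 subjects. The protocol gives no expected split by sex, age or menopausal status, so a count cannot be derived. The group is probably a small share.

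**The case against.** The strongest reply is that little follows in practice, and most of it stands.

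- A reader might infer that criterion 8 cannot be applied at all. The text does not support that. The route for women over 45 with 12 months of amenorrhea works without FSH on the natural reading. Sterilization and other incapacity for pregnancy never need it, and a woman who meets none of these can enroll as of childbearing potential on two methods. Read literally, the unit closes one route.
- A reader might also infer that younger women would be waved through as postmenopausal without hormone evidence, leaving pregnancies unprotected. Nothing in the protocol permits that. Without a qualifying FSH the route is not met, and the woman falls into the childbearing group. The closing note of Section 4.2 requires all criteria to be confirmed before treatment. Every woman has a serum pregnancy test at screening, and Section 9.1.1 allows extra tests at any time.
- Nor does the classification govern a urine test at every visit, since none is scheduled at Weeks 1 and 2.
- Nothing in the document contradicts the printed unit, and Section 4 sends questions about the criteria to the sponsor. Because criterion 8 describes status before screening, an FSH result already on file might serve. The schedule does not forbid testing others.

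These points limit the consequences. They do not remove the mismatch, which can be shown from the protocol alone. They also do not make 40,000 IU/L a plausible cut-off under the usual laboratory convention.

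**Conclusion.** The point holds in limited form and should be corrected.

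The mismatch needs no outside knowledge: criterion 8 sets no upper limit on amenorrhea for women aged 45 or younger, while the schedule stops at 2 years. The unit finding rests on one assumption, that serum FSH is reported in IU/L or mIU/mL. On that assumption the printed threshold is 1000 times too high, and read literally no woman qualifies through FSH.

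The likely effect is misclassification of a few women, mainly in the cautious direction: contraception and pregnancy testing for women who do not need them. A menopausal woman who depends on FSH and does not use two methods would fail criterion 8. Sites may also handle the criterion differently, some silently correcting the unit and others not. The primary endpoint, sample size and power are unaffected.

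**What to change.** 1. Confirm with the central laboratory the unit in which FSH is reported, and correct criterion 8 if the printed unit is a slip.
2. Reconcile criterion 8 with footnote i of the Time and Events Schedule, Part 1, and with Section 9.5.2, so that the women scheduled for FSH are those whose classification depends on it. Make clear whether FSH attaches to one limb of the postmenopausal definition or to both, and define who is tested without presupposing the result.

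Which ages, durations and threshold should apply is a clinical decision for the sponsor. This review does not propose one.

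The cost is a wording change in an amendment, matching text in the laboratory manual if needed, and possibly a few extra FSH assays. FSH is already a screening test. Amendment INT-3 made a comparable laboratory correction, of serum to plasma for insulin and glucose.
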